### Sample Size

Based on a previous study [27], a mean improvement of 2.16 kg, with an estimated standard deviation of 5.2 kg, in handgrip strength is expected; therefore, a minimum of 56 participants (using power=0.8 and α=.05) are needed. When accounting for 10% dropout, a minimum of 63 participants are needed. Given that 7 participating centers are involved, each center aims to include 9 participants, but centers are allowed to include more if they can, up and until the total target sample size is achieved.

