### Statistical Analysis

Outcome measures will be analyzed using SPSS statistical software (version 19; IBM Corp). Data from the 3 baseline assessments (T0, T1, and T2) will be averaged (for overall preassessment values). Statistical analysis of the therapeutic effect will be performed on all participants who completed all assessments up to and including T3 and T4. Data from participants who drop out before or during the intervention period will be analyzed separately to analyze the patient characteristics of dropouts, including the reasons for dropout, to identify potentially relevant information regarding reevaluation of target population, device-related issues, to inform proper interpretation of study outcomes.

Normality of data distribution for each outcome measure will be checked by visual inspection and with the Shapiro-Wilks test, prior to analyzing outcome measures. Descriptive statistics will be used for all outcome measures (mean and standard deviation or median and interquartile range as applicable). The overall level of significance will be set to *P*<.05.

In order to assess the effect of the intervention over time, linear mixed models will be used to analyze changes in outcome measures over time. If a significant difference is found between sessions, multiple comparisons are performed with Sidak posthoc analysis. If data are not normally distributed, logarithmic transformation will first be applied to potentially achieve normally distributed data and enable use of linear mixed models for analyses. Otherwise, the Friedman test will be used for nonparametric analysis.

In addition, correlations (Pearson correlation coefficient or the nonparametric Spearman correlation coefficient, depending on data characteristics) between amount of use (measured by diary, Carbonhand system, or Motor Activity Log) or baseline patient characteristics and change in hand function outcome measures will be calculated to evaluate whether an increased dose or specific patient characteristics are associated with better outcomes

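### The 56 completers do not follow from the stated inputs, and the T3 contrast is tested only as a Sidak-corrected post hoc comparison, with about 74% power if three pairs are compared

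*Protocol article*

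**What the plan says.** Sample Size (protocol article, Methods) gives the planning values: "a mean improvement of 2.16 kg, with an estimated standard deviation of 5.2 kg, in handgrip strength is expected". From these it concludes that "a minimum of 56 participants (using power=0.8 and α=.05) are needed", and then that "When accounting for 10% dropout, a minimum of 63 participants are needed". It does not name the test, say whether it is one- or two-sided, give the number of comparisons, or say whether 5.2 kg is the SD of the change.

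Statistical Analysis averages the three pre-intervention sessions into one baseline value and restricts the effect analysis to completers, "performed on all participants who completed all assessments up to and including T3 and T4". The model is given as "linear mixed models will be used to analyze changes in outcome measures over time". The step that would locate an effect is conditional: "If a significant difference is found between sessions, multiple comparisons are performed with Sidak posthoc analysis". The overall significance level is .05. No contrast is singled out for the primary outcome, and the size of the Sidak family is not given.

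Elsewhere the article is clear about the question. The Introduction asks about the effect of 6 weeks of glove use. Study Procedure places T3 within a week of the end of that period and describes T4, four weeks later, as a check on retention.

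**The concern.** The sample size rests on one change score at alpha .05, with no visible allowance for multiplicity. The analysis tests the same change at a stricter level, as one of several post hoc comparisons, and only after a significant session effect. The contrast that answers the objective therefore shares its alpha with retention comparisons.

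The article describes the trial several times as powered and faults the earlier study for insufficient power. If the operative test of the T3 change falls short of 80% at the stated minimum of 56, that description is not secured. A true 2.16 kg gain could miss significance at T3 because of correction for comparisons that are not the main question.

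**Working it through.** **Inputs.** Mean change 2.16 kg, SD 5.2 kg, alpha .05, power 0.80, 56 completers and 10% dropout, all from Sample Size. Assumed: 5.2 kg is the SD of change from the averaged baseline, and tests are two-sided. Standardised effect d = 2.16 / 5.2 = 0.415.

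**Step 1: the plan's own figure.** For one two-sided pre-post comparison, the normal approximation gives n = ((1.960 + 0.842) / 0.4154)² = 45.5, so 46. The noncentral t gives 48. Neither is 56.
- At 56 completers, d√n = 0.4154 × 7.483 = 3.108. Power is 86.3% (t) or 87.5% (normal).
- One-sided testing needs 36 (normal) or 38 (t).
- Two settings come close to 56, neither of them stated: a Wilcoxon signed-rank test with its minimum relative efficiency of 0.864 (55), and two Sidak comparisons (55 normal, 58 t).
- The dropout step does reproduce: 56 / 0.9 = 62.2, so 63.

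**Step 2: the Sidak level.** The per-comparison alpha is 1 − 0.95^(1/m) for m comparisons. The article does not give m. Averaging T0–T2 leaves three time points and hence three pairs; comparing T3 and T4 each with baseline gives two; treating all five sessions separately gives ten, though that fits poorly with the averaging.

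| m | alpha per comparison | power at 56 (t) | power at 56 (normal) | completers for 80% (t / normal) |
|---|---|---|---|---|
| 1 | 0.0500 | 86.3% | 87.5% | 48 / 46 |
| 2 | 0.0253 | 78.8% | 80.8% | 58 / 55 |
| 3 | 0.0170 | 73.9% | 76.4% | 64 / 61 |
| 10 | 0.0051 | 57.9% | 62.1% | 81 / 77 |

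For m = 3, 64 completers at 10% dropout means 64 / 0.9 = 71.1, so 72 enrolled against 63 planned. If all 63 completed, power for m = 3 would be 79.8% (t).

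**Step 3: the overall test.** The sequence of overall F test and then Sidak was simulated at 56 completers with three time points, an SD of 5.2 kg for every pairwise change, and a T4 effect of 0, 1.08 or 2.16 kg (20,000 runs each).
- With post hoc tests using the pooled model error, power for T3 versus baseline was 75.5%, 74.5% and 75.0%. Without the gate it was 75.6%, 74.9% and 75.2%.
- With separate paired t tests, power with the gate was 73.8%, 72.4% and 73.4%.

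The gate costs about one percentage point at most. The fall from about 86% to about 74% is due to the Sidak level.

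**Step 4: sensitivity to the SD.** With m = 3 and 56 completers, an SD of change of 4.85 kg gives 80.5% power (t) and 4.9 kg gives 79.5%.

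**The case against.** The strongest reply is that the mismatch is partly inferred. The article does not say that all pairs are compared. With two comparisons, T3 and T4 each against baseline, power at 56 is 78.8% to 80.8%, essentially the stated 80%. Since 56 is close to the size for two Sidak comparisons, an unstated allowance cannot be excluded. This stands, and it limits the 74% to the three-pair reading.

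A reader might infer that the stated 80% was calculated for a single comparison at .05 and that the analysis then lowers it to 74%. The documents do not support this: 56 is not the 80% size for that test, and the test behind it is not given. The like-for-like loss for three pairs is from about 86%.

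A second reply is that the overall session test is itself the primary test, with post hoc comparisons only locating the difference. Under the simulation settings above, that test has 90% power if the T4 effect is zero or fully retained, and 79% if it is half retained. But a significant session effect does not by itself show improvement at T3, which is what the Introduction asks about.

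A third reply is that the Introduction and Study Procedure already make T3 the main time point, and that formal naming can be left to an analysis plan that is not shown. The question is indeed clear from those sections. However, the article does fix the test procedure, and that procedure gives the T3 contrast no separate standing.

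It is also true that the procedure is conservative, that keeping Sidak control is legitimate, and that the shortfall disappears at a slightly smaller SD.

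**Conclusion.** The point holds in a limited form. The minimum of 56 does not reproduce from its stated inputs for a single two-sided pre-post comparison (46 to 48), and Sample Size does not say what test it is for. Under the analysis as written, power for the T3 contrast at 56 completers is about 74% with three pairs, with a range of about 79% (two comparisons) to 58% (ten). These figures assume that 5.2 kg is the SD of change and that tests are two-sided; the number of comparisons is inferred. The overall test contributes almost nothing to the loss.

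Severity is moderate. The three-pair shortfall against the stated 80% is about 6 points, and the procedure neither biases the estimate nor inflates the type I error. It is worth correcting because the remedy needs no additional participants.

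**What to change.** In Statistical Analysis, name the change in handgrip strength from averaged baseline (T0–T2) to T3 as the single primary contrast. Estimate it from the mixed model and test it at two-sided 0.05, outside the Sidak family and without requiring a significant overall test. Keep Sidak for T4 versus baseline and T4 versus T3 as secondary comparisons. With the article's own inputs, 56 completers then give about 86% power.

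In Sample Size, state the test, the sidedness, the number of comparisons and whether 5.2 kg is the SD of change, and correct or explain the 56.

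If the Sidak procedure is kept for the primary contrast, state the number of comparisons and restate the power: about 74% at 56 completers for three, or about 64 completers (72 enrolled) to reach 80%.

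The preferred change costs a few sentences, to be settled before the outcome data are analysed, and no extra participants. Its downside is that T4 retention no longer shares the same familywise error control as the T3 contrast.

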### Study Procedure

All health care professionals involved in the study received extensive training prior to the start of the patient recruitment in order to standardize the execution of the study across the different centers. Plenary instruction sessions were scheduled; health care professionals were trained in good clinical practice, execution of the study protocol, in fitting and operating the Carbonhand system, and in explaining (following a standard procedure) the use of the Carbonhand system to the participants. All instructions were also documented in logbooks and manuals, which were provided to the professionals. The latest versions of these documents are maintained on a secure project website.

In total, there are 5 assessments for each participant. Three preassessments (T0, T1, and T2) are scheduled across 3 weeks, as baselines, directly prior to the intervention period. After completing the third baseline session, the Carbonhand system is manually adjusted by the professional to the individual participant. Attention is paid to the correct size of the glove and arm straps, the finger length of the glove, and creating 3 support profiles. In addition, instructions about all aspects of the Carbonhand system are given, demonstrated, and practiced with the participant, until the professionals are confident that the participant knows how to use the system properly at home. In addition to receiving the Carbonhand system, all participants will be provided with a short user manual (in Dutch) and an excerpt from the exercise book [30], in which exercises (functional activities that can be used in the home situation) are described for people with almost complete function of the arm.

During the 6-week intervention period, participants use the Carbonhand system at home. Within 1 week of the end of the intervention period, postassessment (T3) is conducted; 4 weeks later, a follow-up assessment (T4) is conducted, to measure the retention of effects.

Monitoring visits by an independent study monitor are planned for each participating center to ensure the continued protection of participants rights and well-being, to assure protocol adherence, and to verify data integrity during the study in compliance with good clinical practice. All protocol deviations will be filed. We anticipate having 5 monitor visits to each center during the course of the study.

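### T4 is there to measure retention, but the only inference named is Sidak tests of difference; a non-significant T3–T4 test would not show that the gain was kept, and the adjustment costs power

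*Protocol article*

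**What the plan says.** Under Study Procedure, the article gives the last assessment one purpose: "4 weeks later, a follow-up assessment (T4) is conducted, to measure the retention of effects".

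Statistical Analysis first collapses the baseline: "Data from the 3 baseline assessments (T0, T1, and T2) will be averaged (for overall preassessment values". It then states that "linear mixed models will be used to analyze changes in outcome measures over time", and that "If a significant difference is found between sessions, multiple comparisons are performed with Sidak posthoc analysis". The overall significance level is 0.05. The analysis set is completers: the analysis is "performed on all participants who completed all assessments up to and including T3 and T4". If a log transformation does not restore normality, a Friedman test replaces the mixed model. Descriptive summaries are planned for all outcomes.

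The article does not say which comparison answers the retention question, or how a T3–T4 result is to be read. Sample Size plans for one mean improvement in grip strength: 2.16 kg, SD 5.2 kg, power 0.8, alpha .05, giving 56 participants, or 63 with 10% dropout.

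**The concern.** Retention is a statement about how much of the T3 gain is still there at T4. The named procedure tests for differences. Failure to find a T3–T4 difference may mean that little was lost, or that the test could not see the loss. The comparison that bears directly on remaining benefit, T4 against baseline, is not singled out. It is one of several interchangeable post hoc pairs and pays the multiplicity adjustment.

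Two things are at stake. The follow-up result could be inconclusive in a way that supports either account, with T4 different from neither baseline nor T3. And the adjustment falls on the T3 comparison too, which is the one the trial was sized for.

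**Working it through.** **Inputs.** From Sample Size: gain 2.16 kg, SD 5.2 kg, 56 evaluable participants, alpha .05. Assumptions: two-sided tests; three session levels (averaged baseline, T3, T4), because the baseline is averaged; all three pairs compared; the same SD for each pairwise change. The article gives no SD for the T3–T4 change, so it is varied below.

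**The plan's own figure.** A two-sided paired t-test with these inputs needs 48 participants for 80% power. The article does not name its test. Dividing by 0.864, the minimum efficiency of the Wilcoxon signed-rank test, gives 48/0.864 = 55.6, so 56. Dropout: 56/0.9 = 62.2, so 63. Both stated figures are reproduced. A paired t-test at 0.05 with n = 56 has 86% power.

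**Sidak level.** For three pairs, 1 − 0.95^(1/3) = 0.01695. The critical t on 55 degrees of freedom is 2.463.

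**Loss needed for significance.** 2.463 × 5.2/√56 = 1.71 kg, and 1.71/2.16 = 79% of the expected gain.

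**Power for a true 2.16 kg difference at SD 5.2 (noncentral t, n = 56).** 74% at the Sidak level, 86% at 0.05. This applies to T3 minus baseline and, under full retention, to T4 minus baseline. If all five sessions were compared instead (ten pairs, level 0.0051), power would be 58%.

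**Result patterns.** These come from simulation of 56 completers with equal SDs for all three pairwise changes. Percentages are of trials with a significant T3 gain. "Neither" means T4 differs significantly from neither baseline nor T3. "Retained" means T4 differs from baseline and not from T3. Adding the overall F test as a gate changes the figures by about one point or less.

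| SD of all changes | Observed loss needed | Half lost: no significant drop | Half lost: neither | 75% lost: retained | Nothing lost: retained |
|---|---|---|---|---|---|
| 5.2 kg | 1.71 kg (79%) | 76% | 53% | 6% | 82% |
| 4 kg | 1.32 kg (61%) | 64% | 35% | 5% | 94% |
| 3 kg | 0.99 kg (46%) | 40% | 9% | 2% | 98% |

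At SD 5.2 the "neither" pattern also appears in 17% of such trials when nothing is lost and in 41% when three quarters is lost. By itself it does not say which happened.

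**Varying only the T3–T4 SD,** with both baseline comparisons held at 5.2 kg and half the gain lost: "neither" occurs in 53% at 5.2 kg, 0.258/0.748 = 34% at 3.68 kg, and 0.094/0.738 = 13% at 2.6 kg. A significant drop is missed in 22% of such trials even at 2.6 kg (0.162/0.738).

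**Ordered testing at 0.05, SD 5.2.** T3 minus baseline: 86%. Under full retention, both T3 and T4 minus baseline are significant in about 78% of trials, against 60% with Sidak. The 86% for T4 holds only for that test taken alone; with the gate on T3 it is about 78%.

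**The case against.** The strongest reply is that the plan is better than a bare T3–T4 test. T4 against baseline is itself one of the Sidak pairs, and a significant result there is direct evidence of remaining gain. Descriptive summaries and mixed-model estimates also bear on retention. T4 is there to measure, not to support a confirmatory claim; the stated expectation concerns improvement after six weeks of use. Sidak over all pairs is a valid, conservative method, and a condensed article may leave contrast order and intervals to an analysis plan that is not shown.

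Much of this stands, and it limits the point. A reader might infer that the planned tests cannot show any kept effect; T4 against baseline refutes that. A reader might infer that the plan treats a non-significant T3–T4 test as retention; the article never says so. A reader might infer that losing most of the gain would look like keeping it. With 75% lost, the retained pattern appears in only about 6% of trials with a significant T3 gain at SD 5.2. The commonest result is a significant drop with T4 not different from baseline (53% at SD 5.2, about 70% at SD 4, about 83% at SD 3).

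The proposed change does not rescue every case either. With half the gain lost at SD 5.2, T4 minus baseline at 0.05 is still non-significant in about 63% of trials with a significant T3.

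What does not fall away is that the article itself fixes the decision procedure and the purpose of T4, and the two do not match. No analysis plan is needed to see that, or to see the loss of power.

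**Conclusion.** The point holds in limited form. The named inference can show that some gain over baseline remains at T4. It does not show how much of the T3 gain was kept, and a non-significant T3–T4 test is not evidence of retention. Partial loss is where this matters: with half the gain lost, about 53% of trials with a significant T3 gain leave T4 different from neither baseline nor T3 if all SDs are 5.2 kg, about 35% at 4 kg and 9% at 3 kg. The article does not give the T3–T4 SD, so how often this would happen is not known. If T3 and T4 are closely correlated, the problem is much smaller.

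The power loss does not depend on that SD. With the article's own 2.16 kg, 5.2 kg and n = 56, Sidak over three pairs gives about 74% for T3 minus baseline, below the planned 80%, and the same for T4 minus baseline under full retention. That rests on the three-level, all-pairs reading and on a t-based analysis. The change is worth making before analysis; the trial's main question can still be answered without it.

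**What to change.** In Statistical Analysis, replace the all-pairs Sidak step with two ordered contrasts from the same model. Test T3 minus baseline at 0.05. Only if it is significant, test T4 minus baseline at 0.05. Report each with a 95% confidence interval, and describe T4 minus baseline as residual gain over baseline, not as proof that nothing was lost. Report T4 minus T3 as an estimate with its 95% confidence interval, and state that its non-significance will not be read as retention.

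The fixed order keeps the familywise error for the two tests at 0.05. At SD 5.2 and n = 56 it raises T3 power from 74% to 86%, and the chance that both contrasts are significant under full retention from 60% to about 78%.

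The cost is a few sentences and no new data. The downside is that there is no formal T3–T4 test, and T4 is not tested if T3 fails.

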### Outcome Measures

#### Overview

The primary outcome measure of the study is maximal handgrip strength. Secondary outcome measures, related to arm and hand function, functional ability, amount of glove use, pain, and quality of life (Table 1), are only performed on the most affected side. All assessments are estimated to take 1.5 to 2 hours.

During the intervention period, the amount of glove use will be recorded automatically by the Carbonhand system. In addition, participants are asked to keep a diary about daily use of the glove and all activities in which they engage. In order to get a thorough understanding about the experience of the participants of using the Carbonhand system during activities of daily living at home and the user friendliness of the system, semistructured interviews will take place after the intervention period (T3).

**Table 1 table1:** Overview of outcome measures.

Outcome measure	International Classification of Functioning, Disability and Health component	Domain	Assessment
Maximal handgrip strength	Body function	Grip strength	T0-T4
Maximal pinch strength	Body function	Pinch strength	T0-T4
Static grip endurance	Body function	Grip endurance	T0-T4
Action Research Arm Test	Activity	Upper extremity performance	T0-T4
Jebsen-Taylor hand function test	Activity	Fine and gross hand motor skills	T0-T4
Michigan Hand Outcomes Questionnaire–Dutch version	Activity	Self-perceived health state	T0-T4
Motor Activity Log	Activity	Self-perceived upper limb performance	T0-T4
Numeric pain rating scale	Body function	Self-perceived intensity of pain	T0-T4
EuroQol 5 dimension, 5 level	Participation	Self-perceived health-related quality of life	T0-T4
Short-form 36	Participation	Self-perceived quality of life	T0-T4
Glove use data	Activity	Registered amount of use	Intervention period
Diary	Activity	Self-perceived amount of use	Intervention period
Semistructured interview	Activity	Patient’s experiences of Carbonhand use	T3

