Jebsen-Taylor Hand Function Test is a reliable and valid test to evaluate functional hand motor skills in different patient groups and healthy people of various ages [37]. The test consists of 7 different unilateral hand skill tasks related to activities of daily living: (1) writing a sentence of 24 characters, (2) turning over 7.6 cm × 12.7 cm cards, (3) picking up and moving small common objects (eg, paper clips, coins, and bottle caps), (4) stacking checkers (test of eye–hand coordination), (5) simulated feeding (eg, teaspoon with beans), (6) picking up large empty cans, and (7) moving weighted (450 g) cans. The duration of each task will be recorded in seconds and summed for the test score [38].

Michigan Hand Outcomes Questionnaire–Dutch Language Version (a total of 57 items) assesses patients’ opinions their hands and health [39,40]. The questions are used to assess out how patients feel and to what extent they are capable of carrying out daily activities in the past week (with the exception of part 3, in which the last 4 weeks is used). The problem is mapped out within 6 domains: total hand function, activities of daily living, work situation, work performance, pain, aesthetics, and satisfaction. Within each domain, items are scored on a 5-point Likert scale. The scores are normalized to a range of 0 to 100. For the pain scale, higher scores indicate more pain. For the other 5 scales, higher scores indicate better performance.

The Motor Activity Log [41] is a semistructured questionnaire that assesses self-perceived amount of use and quality of movement of the affected arm and hand by stroke patients during activities of daily living. This questionnaire consists of 26 activities and has excellent test-retest reliability for both scores of each activity; each activity is rated by the participant for quality of movement and amount of use of the upper extremity on a 5-point scale.

An 11-point numeric pain rating scale—from 0 (no pain) to 10 (the most intense pain imaginable)—is used to measure the subjective intensity of pain (patients select a value that is most in line with the intensity of pain that they have experienced in the last 24 hours). The numeric pain rating scale has good sensitivity, while producing data that can be statistically analyzed [42].

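### The Motor Activity Log is listed as a measure of dose, but it rates use of the affected arm, not glove exposure, so its correlation with hand function change can resemble a dose-response when glove time has no effect

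*Protocol article*

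**What the plan says.** In the protocol article, the last paragraph of Statistical Analysis plans Pearson or Spearman correlations in addition to the linear mixed models. One side of each correlation is "amount of use (measured by diary, Carbonhand system, or Motor Activity Log", or a baseline characteristic. The other side is hand function: "change in hand function outcome measures will be calculated". The stated purpose is "to evaluate whether an increased dose or specific patient characteristics are associated with better outcomes".

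Elsewhere the article describes the three use measures differently:

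- **Motor Activity Log.** Secondary Outcome Measures says that it "assesses self-perceived amount of use and quality of movement of the affected arm and hand by stroke patients during activities of daily living", and that "each activity is rated by the participant for quality of movement and amount of use of the upper extremity on a 5-point scale". Table 1 gives its domain as "Self-perceived upper limb performance" and schedules it at T0 to T4.
- **Device log.** Table 1 gives its domain as "Registered amount of use", collected during the intervention period.
- **Diary.** Table 1 describes it as the participant's own account of the amount of use, also collected during the intervention period. Secondary Outcome Measures says it records how often and how long the glove system is used each day.

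The Intervention section expresses the recommended intensity as time using the system: at least 180 minutes per week for 6 weeks.

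**The concern.** A dose variable should measure exposure to the intervention. Two of the three listed measures do so. The Motor Activity Log asks about the affected arm and hand in daily life, whether or not the glove is worn, and half of its content is quality of movement. A participant whose hand improves for any reason may well use it more and rate it higher. A correlation between this score and change in hand function can therefore arise without any contribution from the glove.

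The trial has no control group, as the article acknowledges among its challenges. A relation between glove exposure and improvement is one of the few internal signals that could link a change to the device. If a correlation between two outcomes is reported under the name of dose, readers may take it for that signal.

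**Working it through.** The plan states no figure on this point. The check has two parts: a comparison of sections, and an illustration of size.

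**1. Comparison of sections**

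| Measure | What is rated or recorded | When | Measures glove exposure? |
|---|---|---|---|
| Device log | Use of the system (for example, total time switched on) | Intervention period | Yes |
| Diary | Frequency and duration of system use per day | Intervention period | Yes |
| Motor Activity Log | Amount of use and quality of movement of the arm and hand | T0 to T4 | No |

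By the Study Procedure section, the glove is fitted and handed over after the third baseline session. The Motor Activity Log thus has three values (T0, T1, T2) before exposure begins, and another at T4, four weeks after T3. A scale with values before exposure starts is not a measure of that exposure. No section says that participants rate glove use on it.

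Glove time is also a small share of arm use. Assuming 16 waking hours a day, the recommended 180 minutes per week is 180 / (16 × 60 × 7) = 180 / 6,720 = 2.7% of waking time. At the recommended level, the score would mostly reflect arm use without the glove.

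**2. Size**

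Inputs: n=56, the minimum before the dropout allowance (Sample Size section); significance level .05 (Statistical Analysis), taken as two-sided (assumption). The true correlation ρ between the Motor Activity Log measure and change in hand function, for reasons unrelated to the glove, is not in the article, so a range is assumed.

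Critical correlation: with t(.975, 54) = 2.005,

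r = 2.005 / √(2.005² + 54) = 0.263.

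Probability of a significant positive result by Fisher's transformation: Φ(atanh(ρ) × √(n − 3) − 1.96), with √53 = 7.280.

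| Assumed ρ | atanh(ρ) | × 7.280 | minus 1.96 | Φ |
|---|---|---|---|---|
| 0.1 | 0.1003 | 0.730 | −1.230 | 0.109, about 11% |
| 0.2 | 0.2027 | 1.476 | −0.484 | 0.314, about 31% |
| 0.3 | 0.3095 | 2.253 | 0.293 | 0.615, about 62% |
| 0.4 | 0.4236 | 3.084 | 1.124 | 0.870, about 87% |

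A simulation of 20,000 trials of 56 participants agrees. The glove dose effect was set to zero, and change in the Motor Activity Log and change in hand function each loaded equally on a shared improvement. The implied correlation is the loading squared. Loadings of 0, 0.3, 0.5 and 0.7 (implied ρ of 0, 0.09, 0.25 and 0.49) gave significance in 5%, 10%, 47% and 98% of trials.

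The simulation used change in the Motor Activity Log. The article does not say whether change or level, or which of the two scores, would be used. Logged glove time stayed near 5% throughout, but only because it was simulated as unrelated to improvement. That figure is an input, not evidence that the device log is free of confounding.

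**The case against.** The best defence is that the plan speaks of amount of use, not of glove use, and that the Motor Activity Log has an amount-of-use score. The Discussion describes the mechanism as repeated use of the affected arm in daily activities, giving high-dose practice and possibly preventing learned nonuse. On that view total arm use is a proxy for practice dose. This stands as a reason to look at the association. It does not make the score a measure of dose of this intervention, which the article otherwise expresses as minutes of system use, while Table 1 classes the Motor Activity Log as performance.

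It is also fair that glove time is chosen freely by participants, so those who improve may wear the glove more. Device-logged time is not immune to the same ambiguity. The log also records time switched on, which is not the same as active use, and it is cumulative. These points stand and belong in the interpretation, but the log at least measures exposure.

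A reader might infer more than the article supports:

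- **That the whole dose-response analysis is outcome against outcome.** It is not; two of the three measures are genuine exposure measures.
- **That cause and effect are reversed.** This is not shown. Direction is undetermined, and the plan claims only association.
- **That a false dose-response will be declared in 87% of trials.** That figure belongs to one assumed correlation, and looks at the Motor Activity Log regardless of what the other two measures show.
- **That the trial relies on this as its main supporting evidence.** No section says so; the correlations are an addition to the mixed-model analysis.
- **That the word joining the three measures is itself a defect because it permits selection.** It can be read simply as a list, and which measure is primary may be settled in an analysis plan not shown here.

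**Conclusion.** The point holds for one of the three use measures in an additional analysis. As written, the plan treats a self-rated performance outcome as dose, and its correlation with change in hand function can be significant when glove time has no effect. With 56 participants the chance is about 11% to 87% for assumed correlations of 0.1 to 0.4. The exact size depends on that assumption, on a two-sided test and on n=56. Any positive correlation that two outcomes share through improvement, however, lifts the chance above the nominal 5%. The device-log and diary correlations are not affected by this point, and the primary grip-strength result is unchanged. It is worth correcting because the trial is uncontrolled and the label matters to interpretation.

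**What to change.** Take the Motor Activity Log out of the list of use measures in Statistical Analysis and keep it as an outcome. Alternatively, keep the correlations but report them as associations between arm use and hand function, not as a glove dose-response. Base the dose-response on device-recorded total time, with diary minutes in support. State beside the result that glove time is self-chosen, so it too may follow improvement, and that the log records time switched on.

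The cost is a change of one phrase and two sentences of caution. The device log and diary are already collected, so no new data are needed. The article reports data collection as still under way at publication, so at that time the wording could be settled before the final analysis.
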